## Abstract

**Introduction:**

Tourette syndrome is a common, disabling childhood-onset condition. Exposure and response prevention (ERP) is an effective treatment for tics, yet access remains limited due to a shortage of trained therapists and uneven geographical distribution of services. The ORBIT trial demonstrated that internet-delivered ERP is both clinically and cost-effective, but was developed on a university research platform, not suitable for widescale roll-out. To enable adoption by the National Health Service (NHS) in England, ORBIT has been redeveloped on an NHS compliant platform. This study will evaluate the usability, acceptability and preliminary outcomes of ORBIT on the new platform within an NHS tic disorder service.

**Methods and analysis:**

This single-cohort usability study will recruit 20 children and young people (aged 9–17) with tics and their chosen supporters (parents/carers). Participants will receive a 10-week online ERP intervention supported by trained coaches. Outcomes include uptake, adherence, system usability, satisfaction and clinical measures such as the Yale Global Tic Severity Scale, Parent Tic Questionnaire and Goal-Based Outcomes. Qualitative feedback will be collected via semi-structured exit interviews. Usability metrics and adverse events will be monitored throughout.

**Ethics and dissemination:**

The study has received ethical approval from North West Greater Manchester Research Ethics Committee (ref: 25/NW/0107). The findings from the study will inform future NHS adoption. The results will be submitted for publication in peer-reviewed journals.

**Trial registration number:**

ISRCTN82718960. Registered 10 July 2025. https://doi.org/10.1186/ISRCTN82718960

STRENGTHS AND LIMITATIONS OF THIS STUDYEvaluates the real-world usability of a previously validated digital intervention on a new technical platform, providing insights into user experience, real-world outcomes and implementation feasibility.Provides a practical example of post-trial validation, demonstrating how a clinically effective intervention can be transitioned from an academic research platform to a patient-ready product.Patient and public involvement embedded in every stage of the research including platform development.The small sample size (n=20) limits generalisability of findings, although it is appropriate for a usability-focused study.As a single-cohort study without a comparator, the study does not assess performance against other platforms or delivery methods.

## Introduction

 Tourette syndrome (TS) is a common, childhood onset condition that affects up to 1% of children and young people (CYP) and is associated with high levels of comorbidity, significant distress, psychological impairment and reduced quality of life.^1^ Most patients with TS experience co-occurring conditions such as attention deficit hyperactivity disorder, obsessive-compulsive disorder, depression, anxiety and self-injurious behaviour,^2^ making interventions complex.

Evidence-based interventions for the treatment of tics in CYP include pharmacological treatment and behaviour therapy (BT), such as exposure and response prevention (ERP) or habit reversal training (HRT).^3^,^5^ The effectiveness of BT in reducing tics is well established.^1^ A recent randomised controlled trial demonstrated that ERP was as effective as medication in reducing tic severity, with superior maintenance of treatment gains at 3-month follow-up and greater treatment adherence, likely due to fewer adverse effects.^6^ In England, the National Institute for Health and Care Excellence (NICE) set clinical guidelines for the delivery of care across different conditions. Currently, while no NICE guidelines exist for the management of tics in CYP, both European clinical guidelines^4^ and a Health Technology Assessment evidence synthesis^7^ recommend offering BT as a first-line intervention in a stepped-care approach.

Despite these recommendations, only 1 in 5 CYP with TS in the UK are currently able to access BT for tics.^8^ Moreover, many of those who do access treatment often receive fewer than half the recommended number of sessions.^8^ A critical shortage of trained therapists, coupled with uneven service distribution across the UK, presents a major barrier to equitable access to therapy.^8^

Digital health interventions offer a promising solution to close this gap in treatment provision. A recent randomised controlled trial, ‘Online Remote Behavioural Intervention for Tics’ (ORBIT) trial, found that online delivered, therapist supported ERP is clinically and cost effective.^9 10^ ORBIT led to significantly greater reductions in tic severity (16%) compared to an active control condition (psychoeducation, 6%)^10^; an effect that sustained throughout 6-, 12- and 18-month follow-ups.^11^ A process evaluation confirmed that the intervention was implemented with high fidelity and was highly acceptable to participants.^12 13^ Engagement was rated as excellent, with participants completing an average of 7.5/10 chapters and 88.4% of participants reaching the predefined effective treatment threshold of 4 chapters.

A full economic evaluation found that at 18 months, online ERP had a 79% probability of being cost-effective compared with psychoeducation, at a £30 000 per quality-adjusted life year (QALY) threshold.^7^ While ORBIT represents an additional intervention, health economic analysis suggests its integration into the NHS could reduce overall costs by decreasing reliance on less effective services.^14^ Additionally, the therapist-guided format only required an average of 2.5 hours total clinician time per participant, versus 9–10 hours required for face-to-face BT.^7^

Following this trial, NICE has conducted an early value assessment (EVA) of ORBIT and provisionally approved its use in clinical settings while further evidence is generated.^15^ However, the ORBIT intervention was delivered using the Swedish ‘BiP-TiC’ platform^16^ and is currently not available as a patient-ready product delivered on an NHS compliant platform in the UK. To enable future NHS adoption, it is necessary to re-develop the intervention on a UK-based, NHS-compliant platform and evaluate its usability. As such, this study aims to assess the usability, uptake, acceptability and preliminary outcomes of the ORBIT-UK intervention within an NHS tic disorder service. The intervention will be redeveloped from the original ORBIT trial into a clinical product compatible with NHS systems and commissioning pathways, supporting its future adoption and scale-up. This study will provide a practical example of post-trial validation, demonstrating how an effective clinical trial intervention can be transitioned from an academic research platform to a new technical environment while maintaining core components determining clinical effectiveness within a user-centred evaluation.

## Methods and analysis

### Study design

This study is a 10–12 week, single cohort usability study for CYP with tics. Participants will receive 10 weeks of online, remotely delivered, coach-supported behavioural therapy for tics. The study endpoint will be 3 months post completion of baseline measures, when participants will complete the post-intervention measures within 2 weeks of finishing the intervention. The overall study duration will be 13 months (from the first participant enrolled to last post-intervention assessment). The planned recruitment start date is 1 January 2025, with an estimated end date of 21 September 2026. Overall study completion will be 3 March 2027, and findings will be published within 1 year of data collection. See online supplemental file 1 for an overview of the participant pathway through the study.

### Setting

The intervention will be delivered within a single Tic Disorder Service. Patients are referred into this service by community paediatricians or child mental health services.

### Recruitment and Participants

Eligible participants will be recruited from within the Tic Disorder Service and offered the ORBIT intervention. The initial approach will be from a member of the patient’s usual care team within the Tic Disorder Service. Patients (young people) will be provided with an age-appropriate participant information sheet. Parent/carers will be provided with participant information sheets detailing the clinical study and ORBIT intervention.

#### Inclusion criteria

Aged 9 to 17 years: patient confirmed at screening.Suspected or confirmed TS/chronic tic disorder.Including moderate/severe tics: score >15 on the Yale Global Tic Severity Scale (YGTSS) Total Tic Severity Score (TTSS); TTSS score >10 if motor or vocal tics only: Coach will assess this at initial assessment via video conference.Competent to provide written, informed consent (parental consent for child aged <16): referring clinician confirms at screening appointment.Broadband internet access and regular PC/laptop/Mac/mobile device user, with mobile phone SMS: patient confirmed at screening.Clinical suitability for ORBIT-UK confirmed by referrer from the patients’ usual care team. Clinical suitability refers to the clinician’s judgement that ORBIT is an appropriate therapeutic option, based on clinical presentation, motivation to engage and capacity to undertake the intervention.A parent/carer/legal guardian aged 18+ who is willing and able to act as a supporter.

#### Exclusion criteria

Functional tics as primary presentation.Moderate/severe intellectual disability: confirmed through qualitative judgement of the referrer from the patients’ usual care team.Immediate risk to self or others: confirmed through referrer from the patients’ usual care team.Parent or child not able to speak or read/write English: patient confirmed through screening by the referring clinician.

#### Additional Eligibility Criteria (Supporters, Clinicians and Coaches)

Supporters: A supporter can be a parent, caregiver or legal guardian who is 18 years or older and has the capacity to support CYP through the intervention.Clinicians: Only clinicians who appear on the ORBIT site delegation log will be eligible to be approached to be interviewed.Coaches: Only coaches who appear on the ORBIT site delegation log will be eligible to be approached to be interviewed.

### Screening

The healthcare team in the Tic Disorder Service will approach suitable participants and provide them with participant information sheets. Informed consent will be taken at this screening appointment by the usual treating clinician, further details about which are listed under ‘ethics and dissemination’ and consent forms can be viewed in online supplemental file 2. After obtaining informed consent from young people and their supporters, the clinician will log into the ORBIT platform and complete the automated pre-screening filter with details about the young person to confirm eligibility. If successful in passing the filter, the clinician will go on to complete the main screening assessment which includes demographic information of the participant and their supporter. The screening measures will sit securely within the ORBIT platform. The clinician will assist in scheduling a baseline assessment with an assigned ORBIT Coach.

#### Remote Baseline Assessment

During the baseline assessment, CYP and their supporters will virtually meet their ORBIT coach through Microsoft Teams, who will introduce the ORBIT platform to them. Coaches will provide CYP and their supporters with logins and set a start date for intervention (typically within 24–48 hours of the baseline appointment). During this videocall, the ORBIT-UK Coach will complete the YGTSS^17^ with the YP. Coaches will also assist the YP in setting 1–3 Goal Based Outcomes^18^ (GBOs) based on their choice.

#### Intervention

ORBIT is a web-based intervention for CYP with tics, based on ERP. The platform has been developed by Blum Health (https://blumtechgroup.com/) and is designed with age-appropriate visuals, animations and interactive scripts. The intervention comprises 10 online chapters for CYP and parallel chapters for a designated supporter and is designed to last 10–12 weeks.

Each chapter takes approximately 30–45 min to complete and includes psychoeducation, interactive exercises and ERP skills practice.^7 19^

Participants will receive support, guidance and feedback from a coach via in-platform messaging. The primary Coach will be employed by Nottinghamshire Healthcare Foundation Trust (NHCFT) (Band 5 Assistant Psychologist), and the secondary Coach, a University of Nottingham research assistant, will work within NHCFT under an honorary contract. Coaches will be trained in administering the YGTSS, good clinical practice (GCP) and supervised by the NHCFT clinical team. Neither has prior experience delivering behavioural therapy for tic disorders.

Participants typically have contact with their coach several times per week. Both CYP and supporters have separate logins and equal access to the Coach. Optional downloadable resources include a credit and reward scheme, behaviour tracking tools, teacher information handouts and strategies for managing difficult situations. These materials were developed in the previous ORBIT trial^9 10^ and are intended to enhance, but not replace, the core intervention.

### Measures and Outcomes

#### Baseline

As above, during the remote baseline appointment, the coach will complete the YGTSS and set GBOs with the young person. This appointment will last approximately 1 hour. The YGTSS is a semi-structured interview focussing on motor and vocal tic frequency, severity and tic-related impairment over the previous week. The YGTSS produces a TTSS (0–50) and an impairment score (0–50), with higher scores indicating greater severity/impairment.

GBOs will also be set at baseline, which are realistic, intervention-specific goals (eg, ‘to have better control over my tics’). Young people will rate their progress on a 0–10 scale at the end of each chapter, where 0 means no progress and 10 means the goal is fully achieved.

Following this appointment, additional baseline measures will also be collected from participants through the ORBIT-UK platform. Participants must log in and self-complete these measures before the agreed intervention start date. Once complete, the first chapter of the intervention will be automatically made available.

Completed by the Supporter:

The Parent Tic Questionnaire (PTQ)^20^ : The PTQ assesses the number, frequency and intensity of motor and vocal tics in children and adolescents with tics from their parent/carer’s perspective. The PTQ takes under 10 min to complete.

Completed by the Young Person:

The Child and Adolescent Gilles de la Tourette Syndrome-Quality of Life Scale (C&A GTS-QoL).^21^ The C&A GTS-QoL is a measure of health-related quality of life specifically designed for young people with TS to assess psychological, physical, obsessive-compulsive and cognitive domains of quality of life over the last 4 weeks. Scores are calculated for each domain and summed to provide a total score, with higher scores indicating greater impairment in quality of life. This takes approximately 5 min to complete.

#### During the intervention

At the end of each chapter, participants will complete the following measures:

A review of progress towards GBOs.A chapter usability rating.On-going adverse event (AE) reporting, if necessary, through an in-built ‘Report AE’ function.

#### Mid-intervention (week 5)

Supporters will complete the PTQ to give an indication of how the Young Person is coping with their tics.

#### End of the intervention

The end of intervention has been defined as Week 8, based on findings from the previous ORBIT trial that showed most participants reached this stage, and all therapeutic content will have been delivered. At this stage, participants will complete a series of outcome measures including:

Completed by the Supporter:

PTQSystem Usability Scale (SUS).^22^ The SUS is a widely used, 10-item Likert questionnaire designed to assess the usability of a website or platform. This takes under 5 min to complete.ORBIT Satisfaction Questionnaire.^10^ This is an 8-item measure, with responses rated on a 5-point Likert scale and summed to produce a total satisfaction score, where higher scores reflect greater satisfaction with the intervention. This takes under 5 min to complete.

Completed by the Young Person:

GTS-QoL.SUS.ORBIT Satisfaction Questionnaire.

Once a participant has completed all chapters, their coach will schedule a Teams call to administer the YGTSS with the Young Person (Weeks 10–12). After this call, the Coach will fill out the Clinical Global Impressions Improvement Scale to measure global symptom improvement.^23^ This is a 7-point Likert scale that allows the Coach to assess improvement from baseline. Please see table 2 for an overview of all study outcome measures and timepoints.

**Table 2 T2:** Schedule of outcome measures

Months post-enrolment	0	0	0–3	1	2	3	Completed by	Mode of delivery
Time point	Screening	Baseline (Pre-treatment)	Per-Chapter/on-going	Mid-treatment (5 weeks)	8 weeks	10–12 weeks (treatment end)		
Consent	X						S/YP	REDCap
Automated pre-screening filter (Part A)	X						CL	ORBIT platform
Referral form and demographics (Part B)	X						CL	ORBIT platform
PTQ		X		X	X		S	ORBIT platform
YGTSS		X				X	CO/YP	Videocall (Teams)
CGI-I						X	CO	ORBIT platform
GBO		X	X	X	X	X	YP	ORBIT platform
Chapter rating			X	X	X	X	S/YP	ORBIT platform
C&A GTS-QOL		X			X		YP	ORBIT platform
SUS					X		S/YP	ORBIT platform
Adverse effects/side effects		X	X	X	X	X	S/YP	ORBIT platform
ORBIT satisfaction					X		S/YP	ORBIT platform
Exit interview						X	S/YP/CL/CO	Videocall (Teams)

C&A-GTS-QOL, The child and adolescent version of the Gilles de la Tourette Syndrome Quality of Life Scale; CGI-I, The Clinical Global Impressions Improvement Scale; CL, clinician; CO, coach; GBO, Goal Based Outcomes; ORBIT, Online Remote Behavioural Intervention for Tics trial; PTQ, Parent Tic Questionnaire; S, supporter; SUS, System Usability Scale; YGTSS, Yale Global Tic Severity Scale; YP, young person.

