#### Quantitative Analysis

This study evaluates the usability of the ORBIT-UK platform; therefore, analyses of clinical effectiveness are not planned, as ORBIT’s efficacy and cost effectiveness have already been demonstrated.^10 11^

Descriptive statistics will be used to summarise uptake, adherence and outcome measures across time points. Uptake and adherence will be classified as good or poor (table 1). Outcomes will be summarised across time points using means and SD for normally distributed variables, medians (IQR) for skewed variables and frequencies (%) for categorical variables. Changes in outcomes from baseline to follow-up will be quantified by regression models (linear or non-linear, as appropriate). Non-independence due to repeated measures will be addressed using multilevel models or regression with robust standard errors.

As the study does not test treatment effectiveness, missingness will be summarised but not imputed for usability and adherence outcomes; analyses will use observed data only. For exploratory clinical outcomes, sensitivity analyses may be considered using appropriate imputation methods.

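### The post-treatment YGTSS and CGI-I are tied to finishing all chapters in one place and to a calendar window in others; if the chapter trigger is followed, both are seen in full completers only

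*Protocol article*

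**What the plan says.** All references are to the protocol article.

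- **End of the intervention, text.** The YGTSS instruction to coaches is "Once a participant has completed all chapters, their coach will schedule a Teams call to administer the YGTSS", with Weeks 10–12 given in brackets. The CGI-I depends on it: "After this call, the Coach will fill out the Clinical Global Impressions Improvement Scale to measure global symptom improvement". Nothing is said about a participant who stops before the last chapter.
- **End of the intervention, Table 2.** YGTSS and CGI-I are marked in the column headed "10–12 weeks (treatment end"). The table attaches no completion condition.
- **Study design.** The timing is given in two ways in one sentence: "The study endpoint will be 3 months post completion of baseline measures", and then "participants will complete the post-intervention measures within 2 weeks of finishing the intervention". The second has no meaning for someone who never finishes.
- **Other measures.** PTQ, GTS-QoL, SUS and the satisfaction questionnaire are due at Week 8, which the text calls the end of the intervention because most ORBIT participants got that far. GBOs are rated after each chapter and at the scheduled time points in Table 2.
- **Introduction.** On engagement in the earlier ORBIT trial, it reports "participants completing an average of 7.5/10 chapters", with 88.4% reaching the 4-chapter threshold.
- **Quantitative Analysis.** Change from baseline is quantified by regression, no effectiveness analysis is planned, and imputation for clinical outcomes is optional.

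**The concern.** A coach whose family has stopped at, say, chapter 6 cannot tell from the document whether a YGTSS is due. Table 2 suggests that it is. The only direct instruction to the coach says to arrange the call after all chapters are done, and on that instruction this family is never called.

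This matters because stopping early is unlikely to be unrelated to how useful the platform was. If the families who disengage are the ones not assessed, the YGTSS change and the CGI-I reported under Objective 4 describe the families who stayed. The YGTSS is the only interview-based tic measure in the study and the first clinical measure named in the abstract, and the Discussion says that the study's outcomes will feed NICE's evaluation. An assessment that was never sought cannot be recovered at analysis.

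**Working it through.** **The plan's own figure.** The article gives no figure for the share expected to finish all 10 chapters. The nearest is the adherence benchmark in Table 1: 15 or more of 20 finishing at least 4 chapters, said to be expected in 80% of samples when the probability is 0.8. The exact binomial gives P(X ≥ 15 | n = 20, p = 0.8) = 0.804, so that figure reproduces. It concerns 4 chapters, and the YGTSS trigger is 10.

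**Upper bound on full completion.** Inputs from the Introduction: mean 7.5 of 10 chapters, and 88.4% reaching at least 4. Let f be the share finishing all 10. For a fixed mean, f is largest when everyone else has done as little as the figures allow: 0.884 − f at exactly 4 chapters and 0.116 at none.

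- 10f + 4(0.884 − f) + 0 × 0.116 ≤ 7.5
- 6f ≤ 7.5 − 3.536 = 3.964
- f ≤ 3.964 / 6 = 0.661

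Allowing for rounding of the mean (7.45 to 7.55), the bound runs from 0.652 to 0.669. On 20 participants, 0.661 × 20 = 13.2.

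**Less extreme cases.** If non-completers average m chapters, then f = (7.5 − m) / (10 − m).

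| Non-completers' mean chapters (assumed) | Share finishing all 10 | Expected of 20 |
|---|---|---|
| 4 | 0.583 | 11.7 |
| 5 | 0.500 | 10.0 |
| 6 | 0.375 | 7.5 |

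So 13 is an upper bound on the expected count, and lower values are quite possible. It is not a ceiling on what one sample can show: at f = 0.661, 14 or more of 20 would finish with probability 0.46.

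**Effect on the reported change.** With 13 of 20 assessed, the mean over all enrolled is (13/20) × Dc + (7/20) × Dn, where Dc and Dn are the mean gains in completers and non-completers. Neither is given in the documents. Taking Dc = 4 YGTSS points as an assumption:

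| Dn (assumed) | Mean, all enrolled | Completer mean relative to all enrolled |
|---|---|---|
| 0 | 2.60 | 4 / 2.60 = +54% |
| 2 | 2.6 + 0.7 = 3.30 | 4 / 3.30 = +21% |
| 4 | 2.6 + 1.4 = 4.00 | 0% |
| 5 | 2.6 + 1.75 = 4.35 | 4 / 4.35 = −8% |

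The completer mean is too high if those who stop gain less, unbiased if they gain equally, and too low if some stop because they have already improved.

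**The case against.** The strongest reply is that the chapter trigger is loose wording. The same sentence adds Weeks 10–12 in brackets, Table 2 carries no completion condition, and Study design names a 3-month endpoint, so a sensible team would call everyone on time. That may be the intention, but it does not settle the matter. The sentence on the call states its condition plainly, and Study design also contains a completion-linked timing. The conflict itself is the defect.

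A second reply is that Objective 4 speaks of change after completing the platform, so a completers' result may be what is wanted. If so, the article should say so and give the denominator; Table 2 does not read that way.

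A third is that the consequences are limited: effectiveness analysis is ruled out, n = 20 without a comparator is disclosed, and neither Table 1 criterion uses YGTSS or CGI-I. This stands and lowers the severity. The optional imputation is a weaker defence, since it cannot reliably replace outcomes never sought from about 7 of 20.

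A reader might also infer three stronger things that the documents do not support.

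- *That the whole change analysis, or the usability results, become completers-only.* PTQ, GTS-QoL, SUS and satisfaction are due at Week 8, and GBOs do not wait for the last chapter. The rule that "missingness will be summarised but not imputed for usability and adherence outcomes; analyses will use observed data only" removes nobody who answers. Early stoppers may fail to respond, but that is ordinary non-response and not an effect of this trigger.
- *That benefit is certainly overstated, by around half.* The +54% rests on an assumed zero gain in non-completers.
- *That the adherence denominator needs repair.* Table 1 already reproduces on 20, and anyone stopping before chapter 4 already fails the criterion.

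**Conclusion.** The point holds for two outcomes, YGTSS and CGI-I. The article gives incompatible rules for when, and for whom, they are collected. If the chapter trigger is followed, both are observed in full completers only, which at ORBIT-like engagement means at most about 66%, an expected 13 of 20, with about a third or more of participants never called. This assumes that the mean of 7.5 and the 88.4% describe the same participants and that engagement in ORBIT-UK is similar.

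Optimistic selection is a reasonable worry, but neither its size nor its sign is established: under the assumed gains above it runs from +54% to −8%. Severity is moderate. The analysis is exploratory and no benchmark depends on these measures, but the loss cannot be undone after data collection and is cheap to prevent.

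**What to change.** Reconcile Study design, the text under End of the intervention, and Table 2. State that the YGTSS and CGI-I are sought in the 10–12-week window for every enrolled young person, regardless of how many chapters were completed and including those who stopped. Remove completion of all chapters as the condition for scheduling the call. In the results, report how many were assessed, split by completion status, beside the YGTSS change and CGI-I. If a completers' summary is also wanted for Objective 4, label it as such and give its denominator.

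The cost is a wording change and a few extra calls by the existing coaches, about 7 of 20 at the bound above and more if fewer finish. Some early stoppers will decline, so the selection will be reduced and made visible but not removed. The change needs to be in place before post-treatment assessments fall due.
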